**ANTICIPATED BENEFITS**

This study is of direct benefit to participants. All patients will be treated for their initial parasitemia and any additional parasitemia that presents with clinical symptoms. Any patient failing treatment with the treatment drug regimen will be treated with quinine.

At each visit, the patient, parent or guardian will be informed as to the status of their or their child’s health, and the procedures and/or treatments that will occur during that visit and have the right to refuse a procedure or treatment or request transfer to the regular clinic and withdrawal from the study. All patient costs associated with the study will be paid for. Patients with malaria at government clinics receive for free whatever treatment is available in stock at the clinic. Although AL and CQ is the national policy, it is not always available in government clinics. Additionally, patients typically receive their medication and are discharged without further follow up. Participants would have both clinical and laboratory analysis on the prescribed days to ensure clinical resolution and clearance of parasitemia. Transportation and hospitalization during that 42-day period for other illnesses or for outpatient treatment failure will be free of charge. The participants would have to be in the study to receive these additional benefits.

The findings from the study will assist decision making to improve prevention and treatment of malaria in Ethiopia. With universal access to AL in Ethiopia since 2004 and the long-term use of chloroquine for Pv, monitoring for resistance to both these first-line drugs will be paramount. As a country with two first-line drugs, they are currently discussing the use of AL as the first-line treatment for all malaria regardless of the species. Prior to making this costly shift with little empiric evidence, the efficaciousness of AL for Pv needs to be further assessed.

**RISK/BENEFIT RATIO**

This study has minimal risks and significant benefit to the enrolled subjects.

**VULNERABLE POPULATIONS**

**Children**- This minimal risk study includes children. Because this group has minimal natural immunity, this is the group most at risk for severe malaria, so any treatment must be efficacious in this age group. Adequate provisions are made for soliciting the permission of a parent or guardian.

**Non-English speaking participants**- It is imperative to carry out this study in the areas in which malaria is endemic; therefore, it is unavoidable that some participants will be non-English speaking. All consent forms have been translated into Afaan Oromoo and Amharic and back translated into English for accuracy; all explanations of the study procedures and clinical findings will be carried out in the patient’s local language by local staff member.

**INFORMED CONSENT/ PARENTAL PERMISSION PROCESS/ DOCUMENTATION OF INFORMED CONSENT**

Permission will be obtained from parent/ guardian bringing the child or the adult him/herself. Consent, and assent for children 7-17 years of age, will be appropriately documented prior to each patient’s enrollment. As this study is minimal risk, permission from only one parent will be required. A staff member will read the form to the patient and or parent and give them a chance to ask questions. Patients and or parents who are able to sign their name will be asked to sign the consent form. For non-literate persons, a thumbprint will be obtained in lieu of a signature. Children age 7-11 years of age will have a simplified assent form read to them. Details about the study and its benefits and potential risk will be explained to the patients in the language in which they are most fluent. All information regarding the patients will remain confidential to the extent legally possible. Unique numerical identifiers will be used for data entry.

**JUSTIFICATION FOR WAIVER/ ALTERATION OF INFORMED CONSENT**

No justification for waiver or alteration of informed consent is being sought.

There is a large illiterate population in Ethiopia; thus there is a high likelihood that parents may be unable to sign their names. In this case, permission will be documented with a thumbprint as a legally effective signature in Ethiopia, following thorough explanation of the study and its benefits and potential risk to the patients and or parents/guardians in the language in which they are most fluent. A witness who is not involved with enrolling the patients and literate will witness and sign the informed consent.

**ASSENT IMPLEMENTATION PROCESS/ DOCUMENTATION OF ASSENT**

Assent for children age 7-17 years of age will be sought.

**PROTECTION OF PRIVACY AND CONFIDENTIALITY**

**Privacy of individual** Examinations will take place in a private room. Individual data will be reported to the participants and to relevant staff members, and will be recorded in the health card.

**Confidentiality of data** All screening forms and case record forms will be kept in a secured location with access limited to authorized staff members. Unique numerical identifiers will be used for the computer-based data entry and blood samples. Publications will contain only aggregate data. No identifying information will be included.

**EXTRA COSTS TO PARTICIPANTS**

Participants will not incur extra costs through their participation in this study. All examinations, laboratory testing, and medications will be provided free. Participants will be reimbursed for their travel costs. Their participation in the study will require additional visits, so there will be an extra time cost associated with participation.

**REIMBURSEMENTS OR INCENTIVES**

Patients will be reimbursed 35 Ethiopian Birr (50 Birr those children age>6 years accompanied by a parent) per visit for their travel expenses to minimize loss to follow-up and to prevent patients from incurring extra expenses in travel to and from the clinic for the purpose of participating in the study. The travel reimbursement will be given to each participant even if they are in the same family.

# DISSEMINATION, NOTIFICATION AND REPORTING OF RESULTS

**Notifying participants of their individual results**

Participants and their parents will be informed of the results of the malaria smear, hemoglobin level, and clinical assessments at the time of enrollment and at each follow-up visit. Filter paper analysis will be completed only after the study is completed at a reference laboratory. Participants will not be informed of their individual results from these tests.

**Notifying participants of findings**: Participants will not be directly notified of the study findings.

**Anticipated products or inventions resulting from the study and their use**

All results will be disseminated to the national malaria control programs and other appropriate bodies within the Ethiopian Government. We anticipate that the results of this study will be used to inform future changes to the National Malaria Diagnosis and Treatment Guidelines of Ethiopia. In addition, it is anticipated that the evaluators will develop abstracts for presentation at scientific meetings. Finally, one or more detailed manuscripts will be prepared for publication in a peer-reviewed scientific journal.

**Disseminating results to public**

The Ethiopian FMOH regularly disseminates key findings to the general public. This occurs through press releases and by including media reporters in data dissemination workshops with local leaders at the conclusion of each major activity, or sooner as important findings become available. Findings from this proposed study that may be of value to the general public can be disseminated through these existing mechanisms.

**Scientific Peer Review**

The results from this study will be published in at least one summary paper which will be submitted to a peer-review journal. In addition, additional abstracts may be developed from the results of this study.

**Conflicts of Interest**

We have no conflicts of interest.

# ANNEX

### ANNEX I *P. falciparum* treatment outcomes

| **Classification of treatment outcomes for falciparum malaria**  **WHO [5]** |
| --- |
| **Early Treatment Failure (ETF)** |
| - Development of danger signs or severe malaria on day 1, day 2 or day 3 in the presence of parasitemia; - Parasitemia on day 2 higher than day 0 count irrespective of axillary temperature; - Parasitemia on day 3 with axillary temperature ≥37.5 ºC; - Parasitemia on day 3 ≥25% of count on day 0. |
| **Late Treatment Failure (LTF)** |
| ***Late Clinical Failure* (LCF)**   - Development of danger signs or severe malaria after day 3 in the presence of parasitemia, without previously meeting any of the criteria of Early Treatment Failure; - Presence of parasitemia and axillary temperature ≥37.5 ºC or history of fever during the preceding 24 hours from any day between day 4 to day 42, without previously meeting any of the criteria of Early Treatment Failure.   ***Late Parasitological Failure* (LPF)**   - Presence of parasitemia on any day from day 7 to day 42 and axillary temperature <37.5 ºC, without previously meeting any of the criteria of Early Treatment Failure or Late Clinical Failure. |
|
| **Adequate Clinical and Parasitological Response (ACPR)** |
| - Absence of parasitemia on day 42 irrespective of axillary temperature without previously meeting any of the criteria of Early Treatment Failure or Late Clinical Failure or Late Parasitological Failure. |

### ANNEX II *P. vivax* treatment outcomes

| **Definition of treatment outcomes for vivax malaria**  **WHO [4]** |
| --- |
| **Treatment Failure (TF)** |
| - Clinical deterioration due to *P. vivax* illness requiring hospitalization in presence of parasitemia - Presence of parasitemia and axillary temperature ≥37.5oC any time between Day 3 and Day 28 or Day 42 - Presence of parasitemia on any day between day 7 and day 28 or day 42, irrespective of clinical conditions |

### ANNEX III Severe malaria definitions

Definition of severe malaria [32]

Severe manifestations of P. falciparum malaria in adults and children

| **Prognostic valuea** | | | **Frequencya** | |
| --- | --- | --- | --- | --- |
| Children | Adults |  | Children | Adults |
| *Clinical Manifestations* | | | | |
| + | (?)b | Prostration | +++ | +++ |
| +++ | + | Impaired Consciousness | +++ | ++ |
| +++ | +++ | Respiratory Distress (acidotic breathing) | +++ | + |
| + | ++ | Multiple convulsions | +++ | + |
| +++ | +++ | Circulatory collapse | + | + |
| +++ | +++ | Pulmonary edema | +/– | + |
| +++ | ++ | Abnormal bleeding | +/– | + |
| ++ | + | Jaundice | + | +++ |
| + | + | Hemoglobinuria | +/– | + |
| *Laboratory findings* | | | | |
| + | + | Severe anemia | +++ | + |
| +++ | +++ | Hypoglycemia | +++ | ++ |
| +++ | +++ | Acidosis | +++ | ++ |
| +++ | +++ | Hyperlactatemia | +++ | ++ |
| +/– | ++ | Hyperparasitemia | ++ | + |
| ++ | ++ | Renal Impairment | + | +++ |

aOn a scale from + to +++; +/– indicates infrequent occurrence

bData not available

### ANNEX IV Weight for Height Chart

[figure not shown]

### ANNEX V Schedule of follow-up activities

|  | day 0 | day 1 | day 2 | day 3 | day 7 | day 14 | day 21 | day 28 | day 35 | day 42 |
| --- | --- | --- | --- | --- | --- | --- | --- | --- | --- | --- |
| PROCEDURES |  |  |  |  |  |  |  |  |  |  |
| Clinical assessment | X | X | X | X | X | X | X | X | X | X |
| Temperature | X | X | X | X | X | X | X | X | X | X |
| Blood slide for parasites count | X | (X) | X | X | X | X | X | X | X | X |
| Hemoglobin | X |  |  |  | X | X | X | X | X | X |
| Filter paper | X | (X) | (X) | (X) | (X) | (X) | (X) | (X) | (X) | (X) |
| TREATMENT |  |  |  |  |  |  |  |  |  |  |
| Drug to be given | X | X | X |  |  |  |  |  |  |  |
| Rescue treatment |  | (X) | (X) | (X) | (X) | (X) | (X) | (X) | (X) | (X) |

**NOTES:** Parentheses denote conditional or optional activities. On Day 1, the patient should be examined for parasitemia if she or he has any danger sign. Rescue treatment could be given on any day, provided that the patient meets the criteria for treatment failure. Extra days are any days other than regularly scheduled follow-up days when the patient returns to the facility because of recurrence of symptoms. On extra days, blood slides may or may not be routinely taken. Filter paper collection forPCR will be taken on day 0 and on day of treatment failure.

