**Specific Objectives**

1. To measure the clinical and parasitological efficacy of current first-line therapies of AL for uncomplicated *P. falciparum*, by determining the proportion of patients with Early Treatment Failures (ETF), Late Clinical Failures (LCF), Late Parasitological Failures (LPF), or with Adequate Clinical and Parasitological Response (ACPR) during a 42-day follow-up period for *P. falciparum*, (See Annex I for WHO definitions of treatment outcomes for falciparum malaria)
2. To measure the treatment failure of AL and CQ for *P. vivax* infection during a 42-day follow-up period. (See Annex II for WHO definitions of *P. vivax* treatment failures)
3. To differentiate treatment failures with molecular testing and drug levels

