5. After assignment, on day 0, each patient will receive the morning dose of treatment medication under direct observation and will be monitored for vomiting. The patient or parent will be given the evening dose (for AL only) to administer at home. Each patient will return on days 1 and 2 for subsequent doses. Clinical reassessments will be made on days 1- 3, 7, 14, 21, 28, 35, and 42 (see Annex V for a table of scheduled procedures). Participants will be given 35 Ethiopian Birr for each visit to cover their travel expenses (this is enough to cover round-trip transportation by bus to the clinic for one adult; parent traveling with the enrolled child requiring their own seat (age >6 years) will receive 50 Birr). Patients will be advised to return on *any* day during the follow-up period if symptoms return and not to wait for scheduled visit days. Patients who do not present to the facility for follow-up visits will be followed at home. This is standard for in vivo studies based on the WHO protocol, but is not the standard for routine care. Typically, for patients not enrolled in a study, the parent would be given all the doses of the medicine to administer at home, and no follow-up would be scheduled. The parent would be told to return if the child did not improve.

6. Blood films (thick and thin) for parasite count will be obtained and examined at each visit except day 1 and on any other day if the patient spontaneously returns with fever or worsening symptoms. Hemoglobin status will be measured on days 0, 7, 14, 21, 28, 35, and 42. A filter paper blood spot will be collected on days 0 and in case of treatment failure. All molecular testing will be conducted in Addis Ababa, Ethiopia, by Ethiopia Health and Nutrition Research Institute (EHNRI). Blood drug level testing capacity does not currently exist in Ethiopia and will be conducted at CDC Atlanta. All samples will have the study ID number and date of collection, but no other personal identifiers. The logbook that links the study ID number to the patient will be kept at the study site locked in a cabinet when not in use during the study enrollment period. After the completion of the study, this logbook will be stored in a locked cabinet in Addis Ababa at the International Center for AIDS Care and Treatment Program’s office.

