**Adequate Clinical and Parasitological Response (ACPR)**

- Absence of parasitemia on day 28 or 42 irrespective of axillary temperature without previously meeting any of the criteria of Early Treatment Failure or Late Clinical Failure or Late Parasitological Failure

In order to differentiate a recrudescence (same parasite strain) from a newly acquired infection (different parasite strain), a genotypic analysis based on merozoite surface protein-1 (*msp1)*, merozoite surface protein 2 (*msp2)* and glutamate-rich protein (*glurp)* will be performed by PCR for Pf. Additionally, we will characterize microsatellite markers for Pf to differentiate recrudescence from reinfection and potentially assess for drug resistance markers.

**Definition of Treatment Outcomes for *P. vivax* infections, WHO 2002** [4]

Treatment failure defined as:

1. Clinical deterioration due to *P. vivax* illness requiring hospitalization in presence of parasitemia
2. Presence of parasitemia and axillary temperature ≥37.5oC any time between Day 3 and Day 28 or 42
3. Presence of parasitemia on any day between day 7 and day 28 or 42, irrespective of clinical conditions.

*P. vivax* infections that recur after drug treatment can have 1 of 3 etiologies: 1) recrudescence, 2) reinfection, or 3) relapse arising from the dormant liver stage (hypnozoites). In order to differentiate the treatment failures as recrudescence or relapse from a newly acquired infection, a genotypic analysis based on P. vivax circumsporozoite protein (*pvcs*), the merozoite surface protein 1 (*pvmsp1*) and the merozoite surface protein 3-alpha (*pvmsp3-alpha*) will be performed by PCR for Pv. Additionally, we also will characterize microsatellite markers to assess recrudescence from reinfection and for drug resistance markers. Those who fail in the vivax arms will have drug levels tested from the already collected filter paper.

**Valid end-points** include treatment failure, completion of the follow-up period without treatment failure, loss to follow-up, withdrawal from study (voluntary or involuntary, and protocol violation). Loss to follow-up occurs when, despite all reasonable effort, an enrolled patient who does not attend the scheduled visits, cannot be found. Patients who withdraw from the study during the treatment period (days 0-2) will be treated with AL or CQ depending on the species according to the national policy. They will be referred back to the clinic to continue with care.

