# DATA HANDLING AND ANALYSIS

**Data analysis plan, including statistical methodology and planned tables and figures**

SAS 9.1 (Cary, NC) as well as the WHO drug efficacy tools provided at <http://www.who.int/malaria/toolsformonitoring.html> will be used for data management and analysis. Data will be analyzed using two methods: **per protocol analysis**, where patients who were withdrawn from the study or who were lost to follow-up are excluded, and **survival analysis**, where all enrolled patients are included in the analysis until the last day before drop-out. In addition to voluntary withdrawals or treatment non-compliance, patients will be considered for the analysis as withdrawn if the PCR results are unclassifiable.

The final analysis will include:

- A description of the patients screened, and the distribution of the reasons for exclusion.
- A description of the patients included in the study.
- The proportion of patients lost to follow-up or withdrawn and the distribution of reasons for withdrawal.
- The PCR-adjusted and unadjusted proportion of ETF, LCF, LPF, and ACPR in the Pf arm at day 28 and day 42 with 95% confidence intervals using both methods of analysis.
- Both drug-level and PCR-adjusted and unadjusted proportion of treatment failures in each Pv arm at day 28 and day 42 with 95% confidence intervals using both methods of analysis
- Frequency of side effects, severe malaria, anemia, and hospitalizations by treatment arm

**Data collection**: Data will be collected and recorded at the health facility by one of the trained staff members. All data entry forms will be checked for completeness. Laboratorians may complete brief reports on laboratory findings to share with clinicians who will transfer these results to the case report form of the appropriate patient, the laboratory results will be entered into an Excel database.

**Information management and analysis software:** Microsoft Excel (Redmond, Washington) will be used for double entry of laboratory data and clinical data. SAS 9.1 (Cary, NC) will be used for data analysis.

**Data entry, editing, handling, storage and disposition**: Some open-ended data including the names of specific drugs or diagnoses will be coded prior to data entry. A list of standard codes for these fields will be developed by hand once collection of data is complete. All forms will then be coded and checked by 2 different team members.

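### The unclassifiable-PCR withdrawal rule and the PCR-adjusted ETF proportion do not exempt early failures, so a day 1–3 failure to clear can drop out of the efficacy estimate

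*Protocol*

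**What the plan says.** The rules that matter are in the protocol's DATA HANDLING AND ANALYSIS section. It lists among the final analyses "The PCR-adjusted and unadjusted proportion of ETF, LCF, LPF, and ACPR in the Pf arm at day 28 and day 42". For the P. vivax arms it plans failure proportions adjusted and unadjusted for PCR and drug level. Just before that list it states that "patients will be considered for the analysis as withdrawn if the PCR results are unclassifiable". The same paragraph excludes withdrawn patients from the per-protocol analysis and keeps them in the survival analysis only up to the day before they drop out.

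Nothing elsewhere limits this to late failures:

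- Specific Objectives, item 3: "To differentiate treatment failures with molecular testing and drug levels".
- Enrollment Procedures: "A filter paper blood spot will be collected on days 0 and in case of treatment failure".
- Annex V: filter paper "will be taken on day 0 and on day of treatment failure", with conditional marks in the filter-paper row on days 1, 2 and 3.
- END-POINTS, on P. falciparum genotyping: "In order to differentiate a recrudescence (same parasite strain) from a newly acquired infection (different parasite strain), a genotypic analysis", with no earliest day given.

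ETF is defined in END-POINTS and Annex I. One criterion is "Parasitemia on day 2 higher than day 0 count irrespective of axillary temperature". The others are a day-3 count of at least 25% of day 0, day-3 parasitaemia with fever, and danger signs or severe malaria with parasitaemia on days 1–3. Annex II has no ETF class for P. vivax, but febrile parasitaemia counts as failure from day 3.

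**The concern.** PCR adjustment asks whether parasites seen after treatment are the original infection returning or a newly acquired one. That question suits a recurrence. It does not suit an ETF, which occurs on days 1–3 when dosing runs over days 0–2 and which the protocol judges largely against the day-0 count. An ETF is a failure to clear, so no genotyping result, and no absence of one, should change its status.

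The protocol nevertheless sends early failures through the same PCR handling as late ones. Any resulting error has one direction: PCR handling can remove an early failure but cannot add one, so adjusted efficacy can only be pushed upward. The study exists to detect declining efficacy of first-line drugs, and early failure bears directly on that.

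**Working it through.** **1. What happens to an ETF under the written rules**

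- A patient meets an ETF criterion on day 2 or 3. Filter paper is taken that day (Enrollment Procedures, Annex V).
- The day-0 and failure-day spots are genotyped (END-POINTS; no lower day limit).
- *Unclassifiable result:* the patient is counted as withdrawn. Per protocol, the patient is excluded. In the survival analysis, the patient is censored and contributes no event. This follows directly from the text.
- *Different genotype:* END-POINTS describes a different strain as a newly acquired infection. The protocol does not say whether that applies to an ETF, nor whether a new infection is excluded, censored or counted as a success. This route is permitted, not stated.
- *Same genotype:* the patient remains a failure.

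For P. vivax, the withdrawal rule is not restricted by species, so a febrile failure on day 3 with an unclassifiable PCR is handled in the same way.

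**2. The plan's own precision figure**

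Inputs (Sampling, sample size and statistical power): ACPR 90%, 120 per arm, 20% loss, stated exact 95% interval 82.4%–95.1%.

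- Clopper-Pearson for 90/100 gives 82.4%–95.1%, which reproduces the stated interval and implies 100 evaluable patients.
- A 20% loss from 120 leaves 120 × 0.80 = 96. At exactly 90% the interval is then 82.2%–95.2%. The difference is small and does not affect this point. I use 96 below.

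**3. Effect of losing early failures, per protocol**

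Illustration: 96 evaluable and 10 failures, so ACPR = 86/96.

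| Handling | Estimate | Exact 95% interval |
|---|---|---|
| All early failures kept | 86/96 = 89.6% | 81.7%–94.9% |
| One excluded | 86/95 = 90.5% | 82.8%–95.6% |
| One counted as success | 87/96 = 90.6% | 82.9%–95.6% |
| Two excluded | 86/94 = 91.5% | 83.9%–96.3% |
| Three excluded | 86/93 = 92.5% | 85.1%–96.9% |

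Each excluded early failure adds about 1 percentage point (90.5 − 89.6 = 0.9 for the first).

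**4. Effect in the survival analysis**

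With all 120 patients at risk on day 3, one event multiplies the Kaplan-Meier estimate by 119/120. Censoring that patient instead removes the factor and leaves later risk sets unchanged. If day-42 efficacy is 90% with the event counted, it becomes 0.90 × 120/119 = 90.8%, a rise of about 0.8 points.

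**5. How many patients**

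The Introduction cites AL failure in P. falciparum of 0.9% at baseline and 0% in a recent study. 0.9% × 96 = 0.86 patients, for failures of every type. Early failures are a subset, and only some would have an unclassifiable or mismatched PCR, so 0–1 patient is realistic.

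The protocol gives neither an ETF rate nor a rate of unclassifiable or mismatched PCR. Assuming 1–3 ETFs, each with a 5%–30% chance of being lost:

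- Chance that at least one is lost: from 1 − 0.95 = 5% to 1 − 0.70³ = 66%.
- Expected upward shift, at 0.943 points per loss (86/95 − 86/96): from 0.05 × 1 × 0.943 = 0.05 to 0.30 × 3 × 0.943 = 0.85 points.

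**The case against.** The strongest reply is that the list of final analyses describes a four-category outcome table shown twice. ACPR is in the same phrase, and ACPR patients have no failure sample to genotype. On that reading the adjusted ETF proportion changes only because late reinfections leave the denominator, and the ETF count stays the same. The reading is reasonable, and listing ETF there does not prove that early failures are reclassified. It does not cure the withdrawal rule, which is written for any patient with an unclassifiable PCR.

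A reader might infer that the protocol relabels an ETF with a different genotype as a new infection. No section says so, and the Annex V sentence concerns sample collection only. For P. vivax, END-POINTS introduces genotyping for infections that recur, which leans away from applying it to parasites that never cleared. The stronger claim is not supported; what stands is that nothing rules such handling out.

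It can also be said that this detail belongs in a statistical analysis plan or in the WHO analysis tools the protocol names, neither of which is shown. That answers the silence about how new infections are counted. It does not answer a withdrawal rule that the protocol itself fixes without exception.

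Finally, unadjusted results will be reported alongside, so early failures should remain visible. That limits the harm, provided the withdrawal rule applies only to the adjusted analysis. Its wording does not say so.

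**Conclusion.** The concern holds in limited form. Under the stated rule, an ETF, or a febrile P. vivax failure on day 3, with an unclassifiable PCR is removed per protocol and censored in the survival analysis although it is a true failure. Handling a mismatched genotype as a new infection is left open by the text but not prescribed.

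The error can only favour the drug. It is worth about 1 percentage point per patient per protocol, given 96 evaluable patients and 10 failures, and about 0.8 points in the survival analysis with 120 at risk. At the cited AL failure rates, 0–1 P. falciparum patient is likely to be affected. The early-failure count for P. vivax cannot be derived from the document. This does not affect the sample size. It merits correction because the rule is wrong in principle for early failures and the correction is trivial.

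**What to change.** In DATA HANDLING AND ANALYSIS, state that:

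- every ETF, and every P. vivax failure through day 3, counts as a failure in both the adjusted and the unadjusted analyses whatever the PCR result, including unclassifiable;
- PCR reclassification and the unclassifiable-PCR withdrawal rule apply only to failures after day 3, that is P. falciparum LCF and LPF and later P. vivax recurrences.

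The boundary should be day 3 rather than day 7. LCF begins on day 4, so a day-7 boundary would leave an LCF on days 4–6 eligible by class but not by day.

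Filter-paper collection in Annex V and Enrollment Procedures can stay as it is. The cost is one sentence, with no added samples or visits. The only downside is that adjusted efficacy may come out slightly lower.
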